##### Statistical analyses of the secondary hypotheses

In a subgroup analysis, we will only include patients with known symptom onset. To examine time dependency of test sensitivity and specificity, there will be exploratory comparison of subgroups defined by time from symptom onset to sample collection. Sub group differences in sensitivity and specificity measures will be compared descriptively and by calculating odds ratios and 95% CI.

To evaluate the probability of cerebral infarction within false positives, relative frequencies of patients with cerebral infarction in different diagnostic subgroups and odds ratios and 95% CI will be reported.

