#### Secondary study hypotheses

As secondary study hypotheses, we postulate that

- The sensitivity and specificity of the two previously identified biomarkers H-FABP and NT-proBNP in patients with acute stroke is higher the less time has elapsed since the event in the first 24 h after symptom onset.- The main diagnosis of patients identified as false positives by the biomarker combination is non-LVO ischemic cerebral infarction.

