#### Secondary endpoints

Secondary endpoints are

- sensitivity and specificity of the combination of H-FABP and NT-proBNP paired with clinical parameters for LVO diagnosis at different time points after the index event; and- proportion of false-positive patients with ischemic cerebral infarction in all false-positive patients.

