### Statistics

#### Sample size estimation

From internal STEMO data, we know that approximately 14.4% of STEMO patients with stroke alerts have an LVO diagnosis (preliminary study: 260 LVO of 1800 stroke patients). If 800 patients with stroke alarms are included in the study, we can expect about 116 patients to have an LVO diagnosis.

If data from 800 patients are included in the analysis, it is possible to determine a 95% confidence interval for sensitivity ranging from 66.8 to 83.3% if the observed sensitivity is 75%. This confidence interval was calculated using the Clopper-Pearson method and is based on the assumption of a prevalence of LVO of 14.4%. Similarly, with data from 800 patients, it is possible to determine a 95% confidence interval for specificity ranging from 93.3 to 96.7% if the observed specificity is 95%.

Table 1 shows the values for the confidence interval limits in the case of other observed sensitivity and specificity measures.

**Table 1 tab1:** 95% confidence intervals for sensitivity and specificity assuming a prevalence of LVO of 14.4% and including data from 800 patients.

Sensitivity	95% confidence interval
65%	56.0–74.1%
70%	61.3–78.7%
75%	66.8–83.3%
80%	72.3–87.7%
Specificity	95% confidence interval
80%	77.0–83.0%
85%	82.3–87.8%
90%	87.7–92.3%
95%	93.3–96.7%

Sample size estimations were performed using nQuery Advisor 8.0 [nQuery (2017). Sample Size and Power Calculation. “Statsols” (Statistical Solutions Ltd), Cork, Ireland].

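### A graded time hypothesis is examined only through time subgroups; adding a continuous-time model would use the known onset times better, at little cost

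*Protocol article*

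**What the plan says.** Protocol article, Secondary study hypotheses: the sensitivity and specificity of the two biomarkers "is higher the less time has elapsed since the event in the first 24 h after symptom onset". This is a dose-response type of statement, in which less elapsed time goes with better accuracy.

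Protocol article, Statistical analyses of the secondary hypotheses: for this question "we will only include patients with known symptom onset", and within that set "there will be exploratory comparison of subgroups defined by time from symptom onset to sample collection". The method is then fixed: "Sub group differences in sensitivity and specificity measures will be compared descriptively and by calculating odds ratios and 95% CI". The section names neither a trend test nor a model with time as a continuous variable.

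Protocol article, Secondary endpoints: the related endpoint is accuracy "at different time points after the index event", here for the biomarkers together with clinical parameters.

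Protocol article, Sample size estimation: "we can expect about 116 patients to have an LVO diagnosis" among 800. The calculation covers overall sensitivity and specificity only. No effect size, power or sample size is given for the time hypothesis.

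The article disagrees with itself on direction. Aim of the study expects accuracy to rise as time passes after onset, while the secondary hypothesis expects it to be better the earlier the sample.

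**The concern.** The hypothesis concerns how accuracy changes along a time scale, and the analysis is restricted to patients whose position on that scale is known. Cutting the scale into groups then treats everyone within a group as if sampled at the same time. Two consequences follow:

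- Information is discarded, so the time effect is estimated less precisely than the data allow.
- The size, and possibly the apparent direction, of the effect can change with the number and position of the groups.

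This matters here because the article presents ultra-early dynamics as its advantage over earlier biomarker work, and its Discussion calls the cohort with precisely known onset essential. The article also says most patients will present early, so onset-to-sample times are probably skewed and a wide first window could pool much of the range of interest. Sensitivity can be studied only in LVO patients with known onset, a group small enough that waste is hard to afford.

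**Working it through.** **1. Number of LVO patients (the plan's own figure).** The article gives 260 LVO among 1800, so 260/1800 = 14.4%, and 800 × 260/1800 = 115.6. The stated 116 reproduces. Non-LVO: 800 − 116 = 684. The share with known onset is not given. I assume 50% to 100%, that is 58 to 116 LVO patients.

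**2. Analytic loss for a two-group split.** If the continuous analysis has power P at two-sided 5%, the grouped analysis has about Φ((1.96 + z_P) × √ARE − 1.96). The relative efficiency (ARE) of a median split is 0.75 for uniformly distributed time and 2/π = 0.637 for normal (or log-normal, on the log scale) time.

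- Worked case, P = 80%, ARE 2/π: (1.96 + 0.84) × 0.798 − 1.96 = 0.275, and Φ(0.275) = 61%, a loss of 19 points.

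| Continuous power | Loss, uniform | Loss, normal |
|---|---|---|
| 20% | 4 | 6 |
| 30% | 6 | 9 |
| 50% | 10 | 15 |
| 70% | 12 | 19 |
| 80% | 12 | 19 |
| 90% | 10 | 17 |

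**3. Simulation for sensitivity.** Assumptions: x is standardised log time, normally distributed. logit(sensitivity) = 1.2 − b·x, so mean sensitivity is about 75%, one of the article's illustrative values. With b = 0.5, sensitivity is 85% at 1 SD earlier and 67% at 1 SD later than average; with b = 0.7 it is 87% and 62%. Likelihood-ratio tests at two-sided 5%, 1500 replicates.

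| n | b | Continuous | Median split | Unordered tertiles |
|---|---|---|---|---|
| 58 | 0.5 | 36% | 26% | 22% |
| 58 | 0.7 | 59% | 42% | 41% |
| 70 | 0.5 | 43% | 29% | 27% |
| 70 | 0.7 | 67% | 48% | 47% |
| 116 | 0.5 | 60% | 42% | 40% |
| 116 | 0.7 | 87% | 68% | 70% |

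The loss runs from 36 − 26 = 10 points to 60 − 40 = 20 points. A check run with 20,000 replicates agreed to within about 2 points in every cell.

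**4. Other ways of grouping, other shapes.**

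- Ordered tertile score, same model: 28% against 34% continuous (n = 58, b = 0.5), 51% against 61% (n = 116, b = 0.5) and 78% against 86% (n = 116, b = 0.7). Loss about 6 to 10 points.
- Ordered quartile score with uniform time (ARE 0.9375): loss about 2 to 3 points when continuous power is 50% to 90%.
- Right-skewed time with an effect linear in hours, median split: loss about 40 points.
- True step exactly at the median: the linear log-time model does worse, 42% against 56% for the median split (n = 116, b = 0.5) and 70% against 83% (b = 0.7). The larger check run gave 45% against 55%, and 71% against 83%.

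**5. Specificity.** With average specificity 95% and normal log time, a median split costs 8 points (24% to 16%; 350 non-LVO, log odds ratio 0.3 per SD) up to 21 points (70% to 49%; 350 non-LVO, log odds ratio 0.6). With 684 non-LVO the losses are 12 to 20 points. The loss is therefore not peculiar to the small LVO group.

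**6. Absolute level.** With a median split, a contrast of 80% against 70% sensitivity has power 24%, 18% and 14% with 116, 80 and 60 LVO patients. For 85% against 65% it is 71%, 54% and 43%.

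**The case against.** The strongest reply is that nothing here is a powered test. The comparison is labelled exploratory, is reported descriptively with odds ratios and CIs, and carries no power target. This stands: power points serve here only as a measure of lost information.

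Second, subgroups suit the endpoint. Accuracy at different time points is directly estimated by sensitivity and specificity within windows, and the Discussion also speaks of time windows. This stands too, and is why the windows should be kept. It does not answer the hypothesis, which concerns a gradient.

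Third, a detailed analysis plan is promised before the analysis, and the number and position of the cuts may properly be left to it. Their absence is no fault. The article does, however, fix the form of the analysis as a subgroup comparison, and that form carries the information loss wherever the cuts fall.

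Fourth, the shape is unknown. The article calls the very early course of biomarker levels mostly unknown and predicts opposite directions in two places. A linear log-time model is not neutral, and a step at the cut would favour grouping, although a cut placed exactly at the true change is grouping's best case. A spline is only a weak check: at 75% sensitivity, 0.25 × 58 to 0.25 × 116 gives about 15 to 29 test-negative LVO patients.

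A reader might also infer that low power here is caused by the subgrouping. The documents do not support that. Few LVO patients limit either analysis: at the smaller effect above, continuous time itself reaches only 36% to 60%.

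**Conclusion.** The point holds as a modest one. A graded hypothesis is examined only by comparing time groups, which ignores variation within groups and ties the result to the cuts. The harm is reduced precision and cut-point dependence in an exploratory secondary analysis.

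The size is conditional. It is about 10 to 20 power points for a median split or unordered tertiles, and about 6 to 10 for an ordered tertile trend. Both ranges assume a monotone log-time effect, mean sensitivity near 75% and 58 to 116 LVO patients with known onset. Over other plausible time distributions, groupings and base powers it runs from about 2 to about 40.

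A reader might infer that the plan forfeits a fixed 10 to 20 points. The documents give no effect size, time distribution, known-onset share or cuts from which such a figure could be derived, and under a step-shaped effect the sign can reverse.

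**What to change.** First reconcile the direction expected in Aim of the study with that in Secondary study hypotheses.

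Then add to Statistical analyses of the secondary hypotheses, for patients with known onset: the time hypothesis is analysed by logistic regression of the test result (positive or negative) on continuous log onset-to-sample time. Fit it separately in LVO patients (sensitivity) and in non-LVO patients (1 − specificity). Report the odds ratio per doubling of time with its 95% CI, and a spline with few degrees of freedom as a check of shape.

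Keep sensitivity and specificity by time window, with 95% CIs, as the estimates for the secondary endpoint.

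The cost is a few sentences in the analysis plan, with the same patients and data and a method the article already uses for the primary analysis. The downside is an assumption of linearity in log time that the spline can test only weakly in the LVO group.

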Despite the high number of available biomarkers in stroke diagnosis, only a few have shown a sensitivity of more than 50% for stroke in clinical trials, which largely limits their clinical applicability as stand-alone diagnostic tools so far. One approach to solving this dilemma is to try to combine multiple biomarkers in a biomarker panel to gain more useful information (20).

h-fatty acid binding protein has shown potential in differentiating ischemic stroke from stroke mimics due to its rapid release into circulation following the onset of neurological deficits. This biomarker is released from injured cells and has been associated with cellular damage in the brain, making it a promising candidate for early stroke detection (21). NT-proBNP, on the other hand, is a marker of cardiac stress and is elevated in cases of heart failure. Its levels have been observed to rise in patients with acute ischemic stroke, particularly in those with cardioembolic strokes, which are often associated with large vessel occlusions (LVO) (22). Therefore, the combination of these two biomarkers is hypothesized to enhance the accuracy of LVO detection, especially in a prehospital setting where rapid diagnosis is critical for effective treatment.

The vast majority of studies currently underway examine biomarkers in the context of stroke care either after reaching the emergency department or as treatment progresses. A drawback of this method is that these studies do not include patients who are in the very early phase of suffering from stroke symptoms. Changes in concentration of certain biomarkers that may occur exclusively in an early phase are not identified this way.

With LVOCheck-Opti, we aim to address the unmet medical need of prehospital and CT-independent detection of LVO by evaluating a predefined setup of biomarkers. The results of this study will be used to calibrate a point-of-care device which then be tested in a future, independent study.

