## Methods and analysis

### Aim of the study

The LVOCheck-Opti study aims to demonstrate that patients with large vessel occlusion can be identified with at least 93% specificity and 66% sensitivity by measuring two blood biomarkers previously identified in acute stroke patients, H-FABP and NT-proBNP, in conjunction with clinical parameters (21, 22). This is achieved by testing biomarker levels in a very early time window in patients suspected of having a stroke when queried by the dispatch center, regardless of the final diagnosis. The approach taken in the present study to detect LVO is based on data from other previously unpublished studies, for example, Biofast 1 and Biofast 2,^1^ presented at ESOC 2021.^2^

The results will be used to train and optimize the test algorithm used in the LVOCheck POCT (point of care test) device. Subsequently, the device will be evaluated in prehospital use in a study independent of LVOCheck-Opti.

As neuronal cell injury quickly progresses with time after onset, we also expect to find an increase in sensitivity and specificity over time. Most studies examine blood samples drawn at a far later stage after AIS, therefore the dynamic course of biomarker levels in the very early stages of stroke is mostly unknown.

Furthermore, we seek to determine the main diagnosis of false positives. We assume that most patients with a false positive test result suffer from AIS without LVO and not from hemorrhagic stroke or stroke mimic. This would consequently result in a transport and treatment strategy optimized for patients with AIS.

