##### Statistical analysis of the primary hypothesis

The definitive diagnosis for LVO (gold standard) results retrospectively from the information in the doctor’s letter. Multiple binary logistic regression is used for the algorithm to be developed to predict the individual probability of LVO. Dependent variable: definitive LVO diagnosis from the doctor’s letter, independent variables: Biomarkers H-FABP and NT-proBNP, age, gender, and other clinical parameters and symptoms that can be easily and quickly recorded. The primary outcome analysis yields to evaluate the additional diagnostic value of the biomarkers to clinical and patient characteristics. Since this an observational study, relevant characteristics, that are linked to the outcome will be incorporated in the model for the primary analysis. Using multiple regression models, it is possible to evaluate the additional impact of biomarkers on the outcome after including other patient charactertistics. The method for panel selection will largely follow the procedure outlined by Robin et al. (26), employing panelomics. In summary, we will determine the ideal cutoff values through iterative permutation-response calculations utilizing all relevant parameters (26). The cutoff value will be adjusted in 2% quantile increments, with the sensitivity assessed after each change. This process will continue until we reach peak sensitivity with a specificity of over 95%.

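### Time dependency is judged only by separate odds ratios for sensitivity and specificity, which cannot by themselves separate a threshold effect from a change in discrimination

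*Protocol article*

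**What the plan says.** The protocol article's Secondary study hypotheses section postulates that the sensitivity and specificity of the two biomarkers "is higher the less time has elapsed since the event in the first 24 h after symptom onset". The Secondary endpoints section accordingly defines sensitivity and specificity, with clinical parameters, at different times after the event.

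The analysis is in Statistical analyses of the secondary hypotheses. The population is restricted: "In a subgroup analysis, we will only include patients with known symptom onset". Then "there will be exploratory comparison of subgroups defined by time from symptom onset to sample collection", and "Sub group differences in sensitivity and specificity measures will be compared descriptively and by calculating odds ratios and 95% CI". The section does not say which cut-off applies within the subgroups.

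The only cut-off rule is in Statistical analysis of the primary hypothesis: "The cutoff value will be adjusted in 2% quantile increments, with the sensitivity assessed after each change", and "This process will continue until we reach peak sensitivity with a specificity of over 95" percent. It is a single search, with no time-specific version described. Time since onset is not named among the model's independent variables, although that list is open-ended.

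On what is known about levels over time, the Aim of the study section says that "the dynamic course of biomarker levels in the very early stages of stroke is mostly unknown". On use of the results, the Introduction says: "The results of this study will be used to calibrate a point-of-care device".

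**The concern.** The hypothesis says that both measures are better early. At an unchanged cut-off, both can rise only if discrimination improves. The planned comparison uses two threshold-dependent measures, each with its own odds ratio. These respond both to how well the score separates LVO from non-LVO and to where the score distributions lie relative to the cut-off.

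A shift in both groups is plausible on the article's own account. The Introduction describes early release of H-FABP and a rise in NT-proBNP in ischemic stroke generally, not only in LVO, so non-LVO infarcts could shift too. The article does not establish that they do.

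The stake is interpretation. The data are to train and calibrate the device algorithm, so its threshold is still open. It matters whether early samples carry less (or more) information, or carry the same information around a different level. The first is a finding about the markers; the second is a finding about the cut-off. The article also disagrees with itself on direction: the Aim section expects accuracy to rise over time, while the Secondary study hypotheses section expects it to be higher when less time has passed. A pure level shift gives one odds ratio in each direction, so each expectation could cite half of the result.

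**Working it through.** **Inputs from the protocol (Sample size estimation).** 800 patients; LVO prevalence 14.4% (260/1800); planning values of 75% sensitivity and 95% specificity. Expected LVO cases: 800 × 260/1800 = 115.6, which reproduces the stated figure of about 116. The protocol gives no effect size or precision for the time analysis, so there is no figure of its own to reproduce for it.

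**Assumptions, not in the protocol.** The score is normal with equal variance in LVO and non-LVO patients. There are two time groups, early and late, of equal size unless stated. The early level is lower by s SD in both LVO and non-LVO patients. One cut-off c gives 95% specificity over both groups together.

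**Separation at the planning point.** d = z(0.95) + z(0.75) = 1.645 + 0.674 = 2.319 SD. AUC = Φ(d/√2) = 0.949.

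**Common shift, discrimination unchanged.** With the late non-LVO mean at 0, c solves ½Φ(c + s) + ½Φ(c) = 0.95. Then:

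- early specificity Φ(c + s), late specificity Φ(c)
- early sensitivity Φ(d − s − c), late sensitivity Φ(d − c)

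For s = 0.3, c = 1.513:

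- early: specificity Φ(1.813) = 96.5%, sensitivity Φ(0.506) = 69.4%
- late: specificity Φ(1.513) = 93.5%, sensitivity Φ(0.806) = 79.0%
- odds ratios, early versus late: 0.60 for sensitivity, 1.93 for specificity
- AUC is 0.949, and sensitivity at each group's own 95% specificity is 75%, in both groups

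| Shift s | Sensitivity, early vs late | Specificity, early vs late | AUC, both |
|---|---|---|---|
| 0.25 SD | 70.4% vs 78.4% | 96.3% vs 93.7% | 0.949 |
| 0.30 SD | 69.4% vs 79.0% | 96.5% vs 93.5% | 0.949 |
| 0.50 SD | 64.6% vs 80.9% | 97.4% vs 92.6% | 0.949 |
| 1.00 SD | 49.2% vs 83.7% | 99.0% vs 91.0% | 0.949 |

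**Dependence on the mix.** With s = 0.3 and 30%, 50%, 70% or 80% of patients early, early sensitivity is 67.4%, 69.4%, 71.5% or 72.6%. The more early samples there are, the more they set the cut-off.

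**A true early gain.** Let early separation be 0.3 SD larger (d = 2.619, AUC 0.968 versus 0.949), with the early non-LVO level 0.3 SD lower. Sensitivity at the pooled cut-off is 79.0% in both groups (odds ratio 1.00), and specificity is 96.5% versus 93.5%. At each group's own 95% specificity, sensitivity is Φ(2.619 − 1.645) = 83.5% versus 75.0%. The gain shows in specificity only, and its size of 8.5 points at matched specificity appears in neither odds ratio.

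**The case where there is no problem.** If only LVO scores differ, by 0.5 SD, specificity stays at 95% and sensitivity moves from 75.0% to 88.0% while AUC moves from 0.949 to 0.977. The change at the fixed cut-off is then a real change in accuracy.

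**Precision.** With 116/2 = 58 LVO cases per group, before unknown onsets are excluded, the 95% CI for the sensitivity odds ratio extends by a factor of exp(1.96 × √(2/(58 × 0.75 × 0.25))) = 2.3 either way at 75%.

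**The case against.** - **The pooled cut-off is inferred.** The protocol does not state it for the subgroups, and a detailed analysis plan is announced. This stands. But no other cut-off is described, and the measures that the article does fix are threshold-dependent whichever one is used.
- **A common shift cannot imitate the hypothesis.** The hypothesis has both measures higher early, whereas a common shift sends them in opposite directions, which warns an attentive reader. This stands. What is missing is a commitment to read the two together.
- **A reader might infer that a true gain would be hidden.** That goes too far. In the example above it stays visible in specificity. Only sensitivity is flat, and only the size of the gain is lost.
- **A reader might infer that the early window would be reported below the 66% target.** At a 0.3 SD shift a pooled cut-off does not do this: early sensitivity is 67.4% to 72.6% over the mixes tried. A figure of 64.6% at that shift arises only if the cut-off is set on late patients alone. With equal groups it takes a shift near 0.5 SD. The Discussion expects most patients to present with acute symptoms, so early samples would probably dominate the cut-off.
- **A shift in both groups is not shown.** The article calls the early course mostly unknown. Stroke mimics among the LVO-negative patients may not shift, and the score also contains age, gender and symptoms, which dilute a biomarker shift. This stands; every shift size here is an assumption.
- **The measure matches the endpoint.** For a point-of-care test, performance at its operating threshold is a legitimate target. This stands, and it is why a companion measure is needed rather than a replacement.
- **The analysis is exploratory.** This limits the stakes but does not change what the odds ratios can show.

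**Conclusion.** The concern holds in a limited form. The plan's only measures of time dependency are separate subgroup odds ratios for sensitivity and specificity, probably at one cut-off. By themselves these do not distinguish a shift in score level from a change in discrimination, and they do not give the size of a true change. Under the binormal assumptions, with equal groups and a common 0.3 SD shift, the artefact is about 10 points of sensitivity (69.4% versus 79.0%) and 3 points of specificity the other way (96.5% versus 93.5%), at an unchanged AUC of 0.949. It vanishes if only LVO scores move.

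The documents do not support saying that the planned comparison is wrong, that it must conceal a real change, or that the early window is bound to look worse than the target. The matter is worth settling because the results feed device calibration and the addition costs little.

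**What to change.** In Statistical analyses of the secondary hypotheses, or in the analysis plan that implements it:

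1. Keep sensitivity and specificity by time as the secondary endpoint. State that they use the cut-off from the primary analysis and are interpreted jointly, so that opposite movements are reported as a possible threshold effect.
2. Add, as an exploratory companion, AUC and sensitivity at matched specificity by time window, or ROC regression on onset-to-sample time, with bootstrap 95% CIs.
3. Reconcile the direction of the expected time effect between the Aim of the study and the Secondary study hypotheses sections.

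The cost is some wording and a modest amount of analysis on data already planned. The drawback is imprecision: there are at most about 58 LVO cases per window with two equal windows, and fewer once unknown onsets are excluded. The companion estimates should therefore be presented as descriptive.
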